### Secondary Outcomes

The secondary outcomes are listed as follows:

Objective outcome

Total sleep time (TST): time from falling asleep to final awakening (min).Wake time after sleep onset (WASO): total awakening time during sleep (min)Sleep onset latency (SOL): time from bedtime to the initiation of sleep (min).REM sleep/non-REM sleep ratio (%).Deep sleep (N3) time (minutes).Automatically calculated ratio of REM sleep without atonia (RWA) to total REM sleep epochs (%)

Subjective outcome

PDSS-2Pittsburg Sleep QuestionnaireRBDSQ

The sleep index is analyzed using a portable EEG/EOG recording system collected on two consecutive nights within 7 days prior to the intervention and reobtained on one night within 2 days after the 28-day administration of zonisamide, as shown in Figure 2. PDSS-2, Pittsburg sleep questionnaire, and RBDSQ were collected at baseline, 14 days after the administration and 2 days after the 28-day administration. Other clinical evaluation tools such as the Movement Disorder Society (MDS) Unified Parkinson's Disease Rating Scale part 3 and part 4 (32), item “psychosis” and “anxiety” on MDS non-motor rating scale (33), Beck Depression Inventory second edition (34), and Parkinson's Fatigue Scale (35) were performed.

**Figure 2 F2:**
[figure not shown]
Schedule of examinations and procedures.

*Portable EEG/EOG recording system* (SleepGraph; Medical Device Certification Number: 231AHBZX00001000).

A portable recording system (ZA) (SleepGraph®, Proassist Co., Japan) comprises a wire pair of bipolar EEG and EOG electrode leads, and the receiver was used for recording the frontal EEG and EOG (36). The forehead EEG was recorded from Fp1 with the opposite mastoid process (M2) as a reference, and the EOG electrode records not only electromyography (EMG) (high-frequency waves) but also EOG (low-frequency waves) from the two electrodes on the opposite chin muscle and the skin about 1 cm below the eyes. The signals are recorded at a sampling rate of 128 Hz with filters of 0.5–40 Hz for EEG and of 0.5–44 Hz for EOG. The amplified and filtered analog data from the electrodes were converted into digital signals using a 14-bit A/D converter, transmitted to the receiver placed on the bedside, and stored for offline data analysis. Sleep stage scoring based on the forehead EEG signals was shown in the literature (36), and its following sleep measurements as SE, TST, WASO, and SOL in addition to sleep stage structure were calculated according to the AASM rules. When the duration of phasic muscle activity lasts 0.1–5 s, and the amplitude is four times more than that of the background; EMG activity would be occupied more than 50% on the mini-epoch for 3 s. The epoch is defined as RWA, and the ratio of the RWA to total REM sleep epochs is automatically calculated. The portable EEG/EOG recording system, which objectively assesses sleep at home, is a self-applicable and affordable method. The estimated sleep variables were well-correlated between the portable EEG/EOG recording system and polysomnography, and the interscorer reliability for the sleep stage scoring and sleep variables between them was similar in healthy adults in the validation study (37).

### Statistical Analysis

The full analysis set (FAS) is defined as the population excluding any of the following: not meeting the eligibility criteria, having received zonisamide within 3 months prior to the trial patient's consent, or having no data after allocation. The per-protocol set is defined as the population excluding participants who violated a protocol from the FAS. The safety analysis set (SAS) is defined as the population receiving zonisamide. The amount of change in SE after the 28-day administration will be compared between the zonisamide treatment group and the placebo group in FAS regarding the primary endpoint. For the secondary endpoint, the change in the ratio of the RWA to total REM sleep epochs, TST, WASO, SOL, the ratio of REM/non-REM sleep, and deep sleep time or alteration of each score of PDSS-2, Pittsburg sleep questionnaire, or RBDSQ will be statistically compared between the treatment group and placebo group in FAS. Adverse event rates are evaluated between the two groups in SAS. The analysis methods include Student's *t*-test, Welch's test (for normally distributed patients with equal or unequal variances, respectively), or Wilcoxon's rank-sum test (for non-normally distributed patients). Statistical significance is defined as a two-sided *p*-value <0.05.

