### Randomization and Blinding

The patients from the treatment and control groups were randomized in a 1:1 ratio (Figure 1). This study is designed to be single-blind, but the subject allocation was randomized by an independent allocation manager *via* computer-generated block randomization.

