### Intervention

The subjects in the treatment group took zonisamide (25 mg per day) before bedtime for 28 days. If the dosage of the following medications is stable from 2 weeks before enrollment to the initiation of the intervention, both groups are allowed to receive conventional anti-PD medications including L dioxyphenylalanine (L-DOPA), dopamine agonists, catechol-*O*-methyl transferase inhibitors, monoamine oxidase (MAO) inhibitors, and other antiparkinsonian drugs other than zonisamide, tricyclic or tetracyclic antidepressants, antiepileptic agents, reserpine derivative, phenothiazines, butyrophenone drug, sulpiride, or metoclopramide. All these medications were prohibited from new dosing during the clinical trial period, and a constant dose of these medications was maintained during the intervention. The conventional treatment for comorbidity and complications, sleep stabilizers, or other medications related to PD, such as antidementia drugs, antipsychotics, anxiolytics, or selective serotonin uptake inhibitors, will be allowed, but these dosages will be stable during the clinical trial. Supportive care for maintaining PD status such as rehabilitation before the clinical trial participation's consent would be performed; however, surgery such as deep brain stimulation would not be tolerated. The criteria for discontinuing this clinical trial are withdrawal of the trial participation agreement by subjects or their legal representatives, violation of the selection/exclusion criteria, the occurrence of adverse events that make it difficult to continue the clinical trial, and <70% compliance with the medication criteria.

The schedule of the intervention and outcome measurements is shown in Figure 1.

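### The primary analysis set can drop randomised patients, and the trial-exit rules can leave others without the only follow-up sleep recording, so the primary comparison may not rest on everyone randomised

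*Protocol article*

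**What the plan says.** All references are to the protocol article.

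- **Statistical Analysis, FAS.** The FAS is the "population excluding any of the following: not meeting the eligibility criteria", followed by zonisamide use within 3 months before consent, "or having no data after allocation". The second of these is already an exclusion criterion under Participants and Recruitment.
- **Statistical Analysis, primary comparison.** The change in SE "will be compared between the zonisamide treatment group and the placebo group in FAS regarding the primary endpoint". The tests named are Student's t, Welch's and Wilcoxon's rank-sum. Protocol violators are removed from the FAS to form the per-protocol set.
- **Intervention, exit rules.** The list opens with consent: "The criteria for discontinuing this clinical trial are withdrawal of the trial participation agreement by subjects or their legal representatives". It goes on to name "violation of the selection/exclusion criteria, the occurrence of adverse events that make it difficult to continue the clinical trial". Its last ground is poor adherence, which is worded as "<70% compliance with the medication criteria".
- **Secondary Outcomes, measurement schedule.** The portable EEG/EOG recording is made on two nights before treatment and on one night within 2 days after the 28-day course. The day-14 contact adds the sleep questionnaires but no SE.
- **Randomization and Blinding.** "This study is designed to be single-blind". The text does not say which party is blinded.

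**The concern.** Randomisation protects the comparison only if the patients analysed are those randomised, or a subset chosen without regard to treatment. Two stated rules can undo this.

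First, patients can be taken out of the primary set after allocation for ineligibility, with no condition that the judgement be made blind to arm.

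Second, tolerability and adherence can depend on the treatment received, and here they are grounds for leaving the trial itself. Since SE is next measured only after day 28, leaving before then means no primary outcome is recorded. If exits differ between arms in number or in type of patient, the observed difference in SE mixes the effect of zonisamide with the effect of selection.

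**Working it through.** The document states no power, effect size, SD or drop-out rate, so there is no figure to reproduce. The first step is a reading of the rules. The others are illustrations on assumed inputs.

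**Step 1. Who contributes to the primary test**

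| Randomised patient | In FAS by definition? | Observed SE change? |
|---|---|---|
| Found ineligible after allocation | No | Not used |
| Leaves before any post-allocation data | No | No |
| Leaves after the day-14 questionnaires, before the final recording | Yes | None described |
| Compliance below 70% found only at day 28 | Yes | Possibly |
| Reaches the final recording | Yes | Yes |

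The third row matters most: FAS membership does not supply an outcome.

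**Step 2. Difference between completers and all randomised**

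Assume completers on drug gain 5 SE points over placebo, a fraction f of the drug arm leaves, nobody leaves placebo, and leavers' mean change relative to placebo is d.

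Effect in all randomised = (1 − f) × 5 + f × d, so the bias of the completer estimate is f × (5 − d).

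- f = 0.15 (0.15 × 35 = 5.25, about 5 patients), d = 0: 0.85 × 5 = 4.25. Since 5 / 4.25 = 1.18, the overstatement is 18%.
- f = 0.15, d = −5: 4.25 − 0.75 = 3.5. Since 5 / 3.5 = 1.43, the overstatement is 43%.
- f = 0.10 to 0.20, d = 0: bias 0.5 to 1.0 points.
- f = 0.10 to 0.20, d = −5: bias 1.0 to 2.0 points.

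**Step 3. False-positive risk when there is no true effect**

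Assume 35 randomised per arm (70 patients, 1:1) and that those lost tend to be the poor responders, with correlation r between the tendency to leave and SE change. In an arm losing fraction p, the mean among those left shifts by r × φ(z_p) / (1 − p) SD, where φ is the normal density and z_p the normal quantile at p. For p = 0.10 and r = 1 this is 0.195 SD. The bias is the difference in shift between arms. Type I error is approximate, at a two-sided 0.05.

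| Loss, drug vs placebo | r | Bias (SD) | Type I error |
|---|---|---|---|
| 10% vs 0% | 0.3 to 1.0 | 0.06 to 0.19 | 0.057 to 0.125 |
| 20% vs 5% | 0.3 to 1.0 | 0.07 to 0.24 | 0.059 to 0.156 |
| 10% vs 5% | 0.3 to 0.5 | 0.03 to 0.04 | 0.051 to 0.053 |

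**Step 4. Precision**

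The detectable difference at 80% power is (1.96 + 0.84) × √(2/n) SD. With n = 35 per arm it is 0.67 SD. With 20% loss in both arms (n = 28) it is 0.75 SD. Power at 0.68 SD falls from 81% to 72%.

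**The case against.** The strongest defence is that the Statistical Analysis section does not itself drop poor compliers or adverse-event cases. The FAS excludes only ineligible patients, prior zonisamide users and those with no data at all after allocation; other protocol violators leave only the per-protocol set. A patient who exits after day 14 has questionnaire data and stays in the FAS. A reader might infer that the FAS is close to the per-protocol set, but the definitions do not support that. What stands against this defence is that such a patient still has no SE change.

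Other points carry weight:

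- **Timing is uncertain.** The article does not say when compliance is assessed. If that happens at day 28, poor compliers may still be recorded. The schedule figure is not shown, so a recording at discontinuation cannot be ruled out.
- **Only some adverse events count.** The exit rule covers events that make continuing difficult, not every adverse event.
- **Eligibility exclusions can be harmless.** Most criteria are fixed at or before entry, and excluding on them need not bias the result if judged blind and alike in both arms. The Intervention section also gives independent monitoring committees and clinical research associates a role in checking eligibility and violations. It does not say they are blinded, so the gap narrows but remains.
- **Missing-data methods may be in a SAP or full protocol that is not shown.** Their absence from the article is not an error. No analysis method, however, can recover a recording that was never made.
- **The illustrations can mislead.** With d = 0, restricting to completers only inflates a real effect and cannot create a false one. The larger type I errors need one-sided or heavy loss, or strong correlation.

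**Conclusion.** The point holds in a limited form. As written, the primary set can lose randomised patients on an eligibility judgement not required to be blind, and patients who exit before the post-day-28 recording contribute no observed primary outcome. Because these exits follow randomisation and may depend on arm, the primary comparison can be biased.

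A reader might go further and conclude that exits will be unbalanced and that the bias favours zonisamide. The document does not support this: it gives no loss rates by arm and nothing on how leavers fare. The 0.5–2.0 SE points rest on loss of 10–20% in the drug arm only, none on placebo, a 5-point completer effect, and leavers between 0 and 5 points worse than placebo. With loss of 10% versus 5% and modest correlation, type I error stays at 0.051–0.053.

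This should be fixed. Confidence is moderate, given the unseen schedule and the unstated timing of the compliance check.

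**What to change.** (a) Define the primary analysis set as all randomised patients, analysed by assigned arm. Apply eligibility and compliance exclusions to the per-protocol set only.

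(b) In the Intervention section, separate stopping study medication from leaving the trial. Obtain the already planned end-of-treatment EEG/EOG recording and questionnaires, at the planned time, from every patient who has not withdrawn consent, including those who stopped medication or took less than 70% of it. The rules for stopping medication are left as they are.

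The cost is a change of wording and a few home recordings. Some would be made off treatment, so the estimated effect may be smaller. Part (b) helps only patients who have not yet passed the recording window.

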Zonisamide (1,2-benzisoxazole-3-methanesulfonamide) was launched in Japan and was effective for the treatment of PD in clinical trials (21–23). It improved motor symptoms and wearing-off in patients with PD, with a very low incidence of dyskinesia and psychiatric symptoms such as hallucinations (21–23). Its pharmacological mechanisms remain unclear, and the effect of zonisamide on non-motor symptoms was uncertain since the clinical trial has not been studied. More recently, an open-label study showed the efficacy of treatment with zonisamide on PD-specific questionaries in 20 patients with PD receiving 25 mg (60%) and 50 mg (40%) (24). Zonisamide has a long-half life with a low potential for interacting with other medications (25) and its effect may improve the nocturnal motor symptoms, leading to subsequent improvement in sleep disorder. Moreover, in 2012, a patient with PD was reported with vivid nightmares and dream-enacting behavior that was dramatically resolved after treatment with zonisamide (26). In 2015, Ikeda et al. evaluated the therapeutic effects of zonisamide monotherapy in 10 patients with *de novo* PD, and three patients with a prior history of RBD markedly inhibited nocturnal symptoms of RBD after zonisamide treatment (27). These findings raised an open question as to whether zonisamide might have some potential improvement in sleep disorders in patients with PD.

This study aims to verify the safety and efficacy of zonisamide not only for sleep disorders but also for RBD using a mobile two-channel electroencephalography (EEG)/electrooculography (EOG) recording system.

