The exclusion criteria includes the following: patients who had been treated with zonisamide within 3 months prior to obtaining informed consent, with a history of brain surgery including deep brain stimulation surgery, a history of other organic cerebral disorders such as stroke and epilepsy, hepatic or severe renal dysfunction with estimated glomerular filtration rate <30, taking antiepileptic drugs, taking both monoamine oxidase-B (MAO-B) inhibitors and tricyclic antidepressants, severe dyskinesia, severe mental disease, with potential and intention to become pregnant, with a history of malignant syndrome, with suicide attempts, toxic epidermal necrolysis, mucocutaneous ocular syndrome (Stevens–Johnson syndrome) or erythroderma (exfoliative dermatitis), history of hypersensitivity syndrome, interstitial pneumonia, or rhabdomyolysis within 5 years prior to obtaining informed consent, aplastic anemia, agranulocytosis, pure red cell aplasia, or thrombocytopenia, with pacemakers, and a history of hypersensitivity to the components. The subjects who were eligible according to the inclusion criteria provided written consent for participation in this trial.

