To improve adherence to clinical trials, this clinical trial will be regulated to monitor patient safety, adverse effects, quality control of the data, eligibility of patients, and protocol violations by independent monitoring committees and clinical research associates. Moreover, it will be audited thrice during the trial by a professional company unrelated to the research teams. Safety assessment was performed for all subjects through clinical symptoms and features, which were conducted by telephone interview and clinical examination during a visit to the hospital, and was performed thrice at baseline before drug administration, 14 days after drug administration, and during drug administration. When the patients note undesirable and/or unexpected medical findings, which did not occur prior to the clinical trial, it is defined as an adverse effect; the subject will consult the doctor of the trial committee, and the event will be recorded at any time during the course of the trial. The protocol for this trial was approved by the research ethics committee of the Nara Medical University and was registered with the Japan Registry of Clinical Trials (jRCTs051200160).

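### The safety set is defined as zonisamide recipients only, which contradicts the between-group comparison of adverse event rates assigned to that set

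*Protocol article*

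**What the plan says.** The Statistical Analysis section of the protocol article defines three analysis sets and assigns analyses to them. On safety it says: "The safety analysis set (SAS) is defined as the population receiving zonisamide". The next two sentences deal with the primary and secondary endpoints, and the one after them says: "Adverse event rates are evaluated between the two groups in SAS".

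The same paragraph makes clear which groups are meant. Change in sleep efficiency is to be "compared between the zonisamide treatment group and the placebo group in FAS regarding the primary endpoint".

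Elsewhere, the Introduction gives safety as an aim alongside efficacy: "This study aims to verify the safety and efficacy of zonisamide". The Abstract says the same. Under Intervention, the article reports that "Safety assessment was performed for all subjects through clinical symptoms and features".

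**The concern.** A set restricted to people who received zonisamide has no placebo recipients in it, yet a zonisamide-versus-placebo comparison is assigned to that set. An analyst cannot follow both sentences: either the definition is overridden or the comparison is dropped.

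The control arm matters for reading the safety data. The Intervention section counts as an adverse effect any undesirable or unexpected medical finding that was absent before the trial. The Introduction lists hallucinations, psychosis, depression, daytime sleepiness and unsteadiness among the problems that accompany Parkinson's disease or its treatment. Some such events will arise over 28 days whatever the patient takes. Only the rate in concurrent placebo patients shows how many to expect without the drug. If the definition were applied as it stands, the report would give a single-arm listing for an aim that the randomised design was able to address with a control.

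**Working it through.** The article gives no adverse event rate or safety sample-size figure to reproduce. The check is whether the definition and the analysis can both hold, followed by a head count.

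**1. Who receives zonisamide in the trial?** Intervention: "The subjects in the treatment group took zonisamide (25 mg per day) before bedtime for 28 days". The other group is the placebo group.

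**2. Could a placebo patient count as having received zonisamide by another route?**
- Before the trial: the exclusion criteria under Participants and Recruitment rule out "patients who had been treated with zonisamide within 3 months prior to obtaining informed consent". The FAS definition repeats that exclusion.
- During the trial: the permitted background treatment is limited to conventional drugs and "other antiparkinsonian drugs other than zonisamide", so zonisamide is not allowed as a concomitant drug in either group.
- That leaves only a dispensing error, on which no planned comparison can rest.

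**3. Does any other section redefine the safety set?** None does. The definition appears once.

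**4. Head count.**
- Inputs: 70 patients (Participants and Recruitment); 1:1 allocation (Randomization and Blinding).
- Assumption: all 70 are randomised and dosed.
- Per arm: 70 / 2 = 35, give or take any imbalance left by the blocks.

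| Definition of the safety set | Zonisamide | Placebo |
|---|---|---|
| As written: received zonisamide | about 35 | 0 |
| Received at least one dose of zonisamide or placebo | up to about 35 | up to about 35 |

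**5. Consequence.** With x events among n patients in each arm, the risk difference is x_Z/n_Z − x_P/n_P. As written, n_P = 0, so the second term is undefined. So are the risk ratio and any two-sample test. Under the second definition both terms exist.

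**The case against.** The strongest reply is that this is a slip of wording and that zonisamide here stands for study treatment. There is support for that. The Abstract and the Secondary Outcomes section time the follow-up sleep recording by the 28-day administration of zonisamide, although that recording is needed in both arms. The adverse event sentence itself shows that the authors expected both arms to be in the set. As an account of intent this is plausible. It does not remove the conflict. The Statistical Analysis paragraph uses the drug's name literally when it excludes recent zonisamide users from the FAS, and it sets the zonisamide group against the placebo group by name. Even if the loose reading is granted, two points stay open: whether one dose is enough to enter the set, and whether patients are grouped as treated or as randomised.

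Nor is this a detail that an article may leave to an unseen analysis plan. The article states both the definition and the analysis, and the two disagree.

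Two stronger readings are tempting, and the documents support neither.

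- *A reader might infer that the trial will have no controlled safety result.* That follows only if the definition is applied literally. Safety is assessed in all subjects, so the placebo data are collected and the comparison can be made once the set is corrected.
- *A reader might infer that the named tests (Student's t, Welch, Wilcoxon rank-sum) are the plan for adverse event rates and are unsuitable for proportions.* The list is introduced as what the methods include, so it need not be complete, and the test for proportions can properly sit in the analysis plan. A tie-corrected rank-sum test on yes/no data is also essentially the Pearson chi-square test for two proportions.

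It is fair to add that adverse events are not listed among the primary or secondary outcomes.

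**Conclusion.** The point holds as an internal contradiction: the stated between-group safety comparison cannot be carried out in the set to which it is assigned. The count of about 35 against 0 rests on all 70 patients being randomised 1:1 and dosed. Fewer dosed patients would change the 35 but not the 0. The zero measures the clash between the two sentences and does not represent lost data. The reach is limited to the safety analysis, since the primary and secondary efficacy comparisons are made in the FAS. Because safety is a declared aim, the definition should be settled before the adverse event data are analysed.

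**What to change.** Replace the definition with one along these lines: the safety analysis set comprises all randomised patients who received at least one dose of study drug, whether zonisamide or placebo, grouped by the treatment actually received. Keep the adverse event sentence, and state that rates are compared between the zonisamide and placebo arms in this set.

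An optional addition is to name the method. Comparing the number of patients with at least one adverse event by Fisher's exact test, with the risk difference and its 95% confidence interval, would be suitable, but other methods for proportions would serve and the choice can be left to the analysis plan.

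The cost is one sentence of protocol or analysis-plan wording. No extra patients, visits or data are required.

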## Abstract

**Background:** Sleep disorders are one of the most frequent non-motor symptoms of Parkinson's disease (PD), and the efficacy of dopaminergic agents remains controversial. Clinical randomized control trials for the treatment of sleep disorders in PD are limited. Zonisamide (1,2-benzisoxazole-3-methanesulfonamide) improved motor symptoms and wearing-off in patients with PD. Patients with PD were reported to have dream-enacting behavior that was resolved after treatment with zonisamide. This study aimed to verify the safety and efficacy of zonisamide for sleep disorders and rapid eye movement (REM) sleep behavioral disorders using a mobile two-channel electroencephalography (EEG)/electrooculography (EOG) recording system.

**Methods and Analysis:** The present study is a randomized placebo-controlled trial to determine the efficacy of zonisamide for sleep disorders in patients with PD. This study was designed to be single-blind, but the subject allocation is randomized by an independent allocation manager via computer-generated block randomization. The subjects in the treatment group took zonisamide (25 mg per day) before bedtime for 28 days. The sleep index is analyzed using a portable EEG/EOG recording system collected on two consecutive nights within 7 days prior to the intervention and reobtained on one night within 2 days after the 28-day administration of zonisamide. The amount of change in sleep efficiency before and after the 28-day administration will be compared between the zonisamide treatment group and placebo group concerning the primary endpoint. As for the secondary endpoint, the change in the ratio of other sleep parameters, including REM sleep without atonia, or sleep architecture will be evaluated.

**Ethics and Dissemination:** The protocol was approved by the Nara Medical University Certified Review Board (CRB5200002). The trial was notified and registered with the Japan Registry of Clinical Trials (jRCTs051200160). Written informed consent will be obtained from every participant using informed consent approved by the CRB. The results of this trial will be disseminated through peer-reviewed scientific journals.

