## Methods and Analysis

### Participants and Recruitment

The present study is a randomized placebo-controlled trial to determine the efficacy of zonisamide for sleep disorders in patients with PD. All procedures were conducted at the Nara Medical University Hospital in Japan. A total of 70 patients were diagnosed with PD according to the International Parkinson and Movement Disorder Society (MDS) diagnostic criteria (28); however, the decline in the striatal uptake on the dopamine transporter in single-photon emission CT does not matter. All patients ≥41 years during the informed consent procurement have at least one sleep problem among the three of the following items: (1) they answered “Sometimes (2–3 times a week),” “Almost none (once a week),” or “Nothing” on item 1 scored regarding “Did you sleep well last week?”; (2) answered “Sometimes (2–3 times a week),” “Many (4–5 times a week),” or “So much (6–7 times a week)” on another item 2 scored regarding “Did you have a bad day at night?” on the PD Sleep Scale (PDSS)-2 Japanese version (29); or (3) they have a score ≥5 on the 10-item no/yes Sleep Behavior Disorder Screening questionnaire Japanese version (RBDSQ) with a maximum score of 13 (30). The PDSS-2 consists of 15 questions regarding PD-related nocturnal symptoms, and it is widely used as a recommended, valid, and highly reliable scale and the validity and reliability of the Japanese version were established (29). RBDSQ provides greater sensitivity and reasonable specificity for RBD compared with polysomnography (31). A cut-off score of ≥5 points has been found to have high sensitivity, specificity, and reliability in the Japanese population (29). All patients have a Mini-Mental State Examination score of ≥22 to preclude the following instructions. All patients are outpatients with Hoehn and Yahr stages 1 to 4 and received oral levodopa before entry. The regimen and dosage of antiparkinsonian medication were stable for at least 2 weeks prior to clinical trial participation.

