### Primary Outcome

The primary outcome was sleep efficiency (SE), which is the percentage of actual sleep time during sleep (%).

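### The primary test compares change in sleep efficiency without baseline sleep efficiency as a covariate, which loses some precision and over-corrects chance baseline imbalance

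*Protocol article*

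**What the plan says.** The outcome (Primary Outcome): "The primary outcome was sleep efficiency (SE), which is the percentage of actual sleep time during sleep".

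The comparison (Statistical Analysis): "The amount of change in SE after the 28-day administration will be compared between the zonisamide treatment group and the placebo group in FAS". The Abstract makes clear that the change is from before to after treatment: "The amount of change in sleep efficiency before and after the 28-day administration will be compared between the zonisamide treatment group and placebo group".

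The tests (Statistical Analysis) are Student's t-test, "Welch's test (for normally distributed patients with equal or unequal variances, respectively), or Wilcoxon's rank-sum test (for non-normally distributed patients"). The same list serves the secondary outcomes, which are also compared as changes. No model with a baseline covariate is named.

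The data (Secondary Outcomes): baseline recordings are "collected on two consecutive nights within 7 days prior to the intervention", followed by one night after the 28 days. The article does not say how the two nights form the baseline value.

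The size: "A total of 70 patients were diagnosed with PD" and "The patients from the treatment and control groups were randomized in a 1:1 ratio", so about 35 per arm. Randomization and Blinding describes block randomisation and mentions no stratification.

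**The concern.** A change score assumes that one unit of baseline difference predicts exactly one unit of follow-up difference. SE varies from night to night, so the regression of follow-up on baseline will usually have a slope below 1. Subtracting the whole baseline then has two effects. It carries baseline noise into the outcome, which widens the standard error. It also moves the estimate too far whenever the arms differ at baseline: the arm that happens to start with worse SE tends to show the larger improvement through regression to the mean.

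In a trial of about 35 per arm, baseline differences of a few tenths of an SD are ordinary. What is at stake is some power, and an estimate that is off in a predictable direction once the baseline table is known. Both can be recovered from data the trial already collects.

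**Working it through.** **Inputs from the article.** N = 70, allocation 1:1, hence 35 per arm; two-sided 5% level; two baseline nights and one follow-up night; two-sample tests on change. The article states no effect size, SD, power or correlation, so it has no figure to reproduce.

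**Assumptions.** Single-night SD = 1 at both visits. Correlation r between the two baseline nights and q between a baseline night and the follow-up night. In setting A all nights are equally correlated (q = r), over 0.3 to 0.8. In setting B, q is lower than r.

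**Formulas.**
- One baseline night: Var(change) = 2(1 − r); Var(ANCOVA) = 1 − r²; ratio = (1 + r)/2.
- Mean of two baseline nights: baseline variance b = (1 + r)/2; Var(change) = 1 + b − 2q; Var(ANCOVA) = 1 − q²/b; slope = q/b.
- If the change-score test has 80% power, ANCOVA has power Φ(2.80/√ratio − 1.96), where 2.80 = 1.96 + 0.84. Equivalent N = 70 × ratio, rounded up.

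**Setting A, mean of two nights**

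| r | Var(change) | Var(ANCOVA) | Ratio | Slope | Power, from 80% | Equivalent N |
|---|---|---|---|---|---|---|
| 0.3 | 1.050 | 0.862 | 0.82 | 0.46 | 87% | 58 |
| 0.5 | 0.750 | 0.667 | 0.89 | 0.67 | 84% | 63 |
| 0.7 | 0.450 | 0.424 | 0.94 | 0.82 | 82% | 66 |
| 0.8 | 0.300 | 0.289 | 0.96 | 0.89 | 81.5% | 68 |

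**Setting A, one night.** Ratios at r = 0.3, 0.5, 0.7 and 0.8 are 0.65, 0.75, 0.85 and 0.90. Power is 93.5%, 90%, 86% and 84%, and the equivalent N is 46, 53, 60 and 63.

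**Setting B, mean of two nights**
- (r, q) = (0.5, 0.35): b = 0.75; 1.05 against 0.837; ratio 0.797.
- (0.6, 0.5): b = 0.80; 0.80 against 0.688; ratio 0.859.
- (0.7, 0.6): b = 0.85; 0.65 against 0.576; ratio 0.887.

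The saving in setting B is thus about 11-20%.

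**Chance imbalance.** The baseline difference between arms has a standard error of √(2/35) = 0.24 SD of the baseline measure, so a 95% range of ±1.96 × 0.24 = ±0.47 SD. Given an imbalance of 0.25 single-night SD, the change-score estimate is off by −(1 − slope) × 0.25. At r = 0.3, 0.5 and 0.7 this is:
- One night (slope = r): −0.175, −0.125, −0.075 SD.
- Mean of two nights (slopes 0.46, 0.67, 0.82): −0.13, −0.08, −0.04 SD.

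The negative sign means that the arm with the higher baseline looks less improved than it should.

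**Simulation check** (4,000 trials per setting, 35 per arm, two-night mean, setting A). With no effect, rejection rates at r = 0.3, 0.5 and 0.7 were 0.049, 0.051 and 0.052 for the t-test on change, and 0.051, 0.053 and 0.049 for ANCOVA. With the effect set for a nominal 80%, power went from 78% to 85%, from 79% to 83%, and from 80% to 81%. The formulas above use a normal approximation and run slightly high.

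**The case against.** The strongest reply is that nothing here is invalid. Under 1:1 randomisation the comparison of change scores is unbiased over repeated randomisations, its standard error already allows for chance imbalance, and the simulated type I error is about 5%. That stands.

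A reader might infer from the plan that baseline SE is ignored and imbalance left uncorrected. The documents do not support this: the Abstract and Statistical Analysis define a before-to-after change, so baseline is used, with a fixed slope of 1, and imbalance is over-corrected.

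A reader might also infer that the slope must be far below 1 and the gain large. The article gives no correlation to support that. At r = 0.8 with averaged nights the slope is 0.89 and the saving about 4%. The larger figures need either weaker correlation or a one-night baseline.

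Two further points have weight. The list of tests is not worded as exhaustive, the article is condensed, and the SAP is not shown, so an adjusted analysis may exist. The article does, however, name the comparison and the tests, and every named test is unadjusted. Secondly, the plan provides a rank-sum test for non-normal data, and outcomes such as sleep latency, wake time after sleep onset and the REM-without-atonia ratio may well be skewed. A linear model imposed on all of them would remove that provision, so the remedy must keep an equivalent.

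**Conclusion.** The point holds as a modest and inexpensive improvement in efficiency that should be made; it is not an error that threatens validity. The direction is secure: with equal arms, ANCOVA is no less precise than the change score apart from one degree of freedom, and it removes the error conditional on baseline imbalance.

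The size rests on assumed correlations, and also on how the two baseline nights are combined, which the article leaves open:
- equal correlation of 0.3 to 0.8, nights averaged: about 4-18% of the variance;
- the same, one night only: about 10-35%;
- across-visit correlation below within-visit correlation, nights averaged: about 11-20%.

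**What to change.** Make the primary analysis an ANCOVA of end-of-treatment SE on arm, with baseline SE as covariate, and report the adjusted mean difference with its 95% CI and p-value. Using change in SE as the response gives the same treatment estimate once baseline is in the model, so the endpoint can still be described as change. Define the baseline value in advance from the two nights, for example as their mean.

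Use the same approach for each continuous secondary outcome, with that outcome's own baseline. Where an outcome is clearly non-normal, use a rank-based or robust baseline-adjusted analysis (for example rank ANCOVA) in place of the plain rank-sum test.

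The cost is one degree of freedom (67 residual instead of 68 with 70 patients), a few sentences in the plan and slightly more analysis work. No new data are needed.
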